### ④ Sample size

The primary outcome indicator in this study is the level of decisional conflict at one month after baseline, which is a continuous variable. For the comparison of continuous variable outcome indicators in randomized clinical trials, the sample size can be estimated by the following equation.

Sample size of each group:

$$n = \frac{{2 \times {{({z_{(1 - \alpha /2)}} + {z_\beta })}^2}}}{{{{(\frac{\Delta }{\sigma })}^2}}}$$

Among them, α is set to 0.05, the Z_(1−α/2)_ takes the value of 1.96, while β is set to 0.80, and Z_β_ takes the value of 0.84. ∆/σ is the effect value and is set to 0.3 with reference to previous literature [37], resulting in a required sample size of 174 participants per group. Considering that some of the study participants (assumed to be ≤ 15%) might drop out of the study, the total target of recruiting participants is set at 410 after appropriate expansion of the sample size, and the intervention and control groups are assigned in a 1:1 ratio.

### ⑤ Intervention

Participants in **the control group** will receive stepped care as in routine services (see study site section for details), including PND screening, health education, on-site counseling and MDT services, and off-site specialty referrals.

Participants in the intervention group will receive the IP-SDM care model developed in this study. The IP-SDM care model will provide expectant and new mothers who have screened positive for PND with the patient decision aid, decision coaching, and on-site outpatient counseling services. To establish and implement the IP-SDM care model, the research team will first train nurses specialized in perinatal mental health and obstetricians who provide on-site outpatient counseling services with how to use the patient decision aid to facilitate SDM between patients (including their families) and maternal care and mental health professionals. During the study, the use of the IP-SDM toolkit within the team will be fluid and dependent on the usual roles and processes of care and the needs of the patient. Specifically, participants in **the intervention group** will receive the following interventions in addition to the usual services.

**Patient Decision Aid**: Participants in the intervention group will receive a patient decision aid for PND prior to their clinical consultation. The patient decision aid will be distributed as a paper booklet, similar in size to the educational materials on perinatal mental health that are routinely distributed at the study site. The patient decision aid will support patients to identify their decision-making problems, understand treatment alternatives, and support them to discuss PND screening results and treatment options with maternal care and mental health professionals, and facilitate SDM.**Decision Coaching**: One week after the clinical consultation, the mother will receive a telephone call back from the mental health nurse, during which the nurse will counsel the patient on decision making based on the IP-SDM model. Specific components include identifying decision problems, exchanging evidence-based information, clarifying the patient’s values and preferences, assessing the feasibility of possible treatment modalities, and evaluating preferred options with the patient. The nurse’s decision coaching will also be available to family members if the patient agrees and requires it.**Clinical Consultation**: If patients attend the study site’s mental health clinic and the joint psychological specialist clinic, the clinician will also conduct a shared decision-making process with the attending pregnant and postpartum women, following the steps in the IP-SDM model. This process will also engage the family if the patient agrees and requires it.

Mental health nurses at the study site, as well as physicians in the mental health clinic and joint psychiatric specialist clinic, will receive training on the implementation of the IP-SDM model, including how to use decision aids with patients and how to provide decision support to patients in decision coaching and clinical consultation. In addition to the training, the research team will develop communication scripts prepared in a step-by-step decision-making process to help health care providers deliver standardized interventions and thereby prevent “contamination” of interventions.

### ⑥ Measurements

This trial will observe for a period of six months after baseline. Except for the questionnaire on hospital costs, which will be administered to relevant medical staff and hospital administrators, all other questionnaires will be administered to participants. The baseline survey will be conducted face-to-face, while the follow-up survey will be conducted over the telephone. A face-to-face or online survey can also be arranged if needed. The survey questionnaire will be made into an electronic questionnaire to facilitate completion by either the researcher or the participant. The main indicators (except basic personal information) and measurement methods in each survey are shown in Table 1. The timeline of assessments is shown in Fig. 3.

**Table 1 Tab1:** Main indicators and measurement methods in previous assessments

Main indicators		Measurement Method
**Primary outcome indicators**		
	Quality of decision-making process	The core indicator of quality of decision-making process is the decisional conflict, i.e. the inner uncertainty of the patient about the treatment option to be chosen during the medical activity. The level of decisional conflict will be measured by the Decisional Conflict Scale (DCS). This scale is the most widely used tool for evaluating decisional conflict and consists of five dimensions: informed, i.e., the extent to which patients understand the potential benefits and risks of the options available to them; value clarification, i.e., the extent to which patients are clear about their values (to measure the benefits and risks); decision support, i.e., the extent to which patients feel supported in their decision; uncertainty, i.e., the extent to which patients are certain about the decision being made; decision validity, which is the patient’s perceived effectiveness, or satisfaction, with the decision. The Chinese version of the scale has also been widely used in studies with good reliability and validity.
**Secondary outcome indicators**		
	Shared decision-making	Shared decision-making will be measured based on an adapted decision expectancy scale (control preference scale, CPS). This scale was originally used to measure patients’ willingness to participate in health care decision-making. In its adaptation, it can also measure patients’ actual participation in decision making in a given decision situation and can classify patients into three types: active decision makers, negative decision makers, and shared decision makers. This is one of the most commonly used and concise tools for measuring shared decision-making.
	Mental health service utilization	A self-administered questionnaire will be used to investigate whether mothers are diagnosed by a psychiatrist with a mental disorder such as PND and the utilization of subsequent mental health services, including all mental health services such as counseling, psychotherapy, and psychiatric services received by mothers at the study site and other institutions or settings (e.g., number of visits, number of counseling sessions, length of medication, etc.).
	Cost	A self-administered questionnaire will be used to measure the costs associated with maternal mental health service seeking. The self-administered scale will be developed with reference to the Treatment Inventory of Costs in Psychiatric Patients and will consist of: direct medical costs, including the costs of maternal psychiatric services, psychotherapy, counseling, etc. (including maternal and health insurance paid costs); direct non-medical costs, including transportation and accommodation fees for maternity and their companions seeking mental health services; indirect costs, including labor losses such as lost wages for maternity and their companions as a result of seeking mental health services. As the related costs are incurred within six months, no discounting is required. Self-administered questionnaires will also be used to measure the cost of conducting the interprofessional shared decision-making model and subsequent mental health services, including mainly depreciation of fixed assets and staff labor costs, among medical staff and hospital administrators.
	Depressive symptoms	Women’s depressive symptoms will be measured by the EPDS, a 10-item maternal self-report of depression over the past 7 days. Higher EPDS scores indicate more severe depression. The EPDS is the most commonly used screening tool for perinatal depression in maternal health care and has good reliability.
	Health-related quality of life	Health-related quality of life will be measured based on the SF-6D, a utility measurement tool created based on the MOS 36-item short-form health survey (SF-36), which is widely used to measure health-related quality of life and can be used to calculate utility values. The SF-6D health classification system consists of 6 dimensions: somatic functioning, role limitation, social functioning, pain, mental health, and vitality. Previous literature has shown that the SF-6D works well in measuring health-related quality of life in mental health and that the SF-6D is more likely to capture the effects of interventions than the EQ-5D in the area of perinatal mental health.

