While decision aid and decision coaching are effective ways to provide decision support to patients and promote SDM, studies related to SDM in mental health are primarily based on populations from high-income countries. Evidence shows that using a decision aid in the treatment of PND is feasible and acceptable, and may reduce decisional conflict [26, 27]. However, further research is warranted to examine its impact on mental health service utilization and depression outcomes [28, 29] and its implementation in primary care settings. There is still a lack of decision aid for perinatal depression as well as an SDM model involving multiple stakeholders for the Chinese population. Moreover, as the impact of SDM on healthcare resource consumption remains controversial, it is warranted to conduct an economic evaluation to assess the cost-effectiveness along with the effectiveness of implementing SDM for perinatal depression in China’s healthcare system.

This study aims to design a decision aid tailored to Chinese patients with perinatal depression. The decision aid will serve as the centerpiece for developing a novel shared decision-making model that integrates multiple parties, such as multi-specialty and multi-professional medical personnel, patients, and their families. The study hypothesizes that this model would have a positive impact on the quality of the decision-making process, mental health service utilization, and mental health outcomes.

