#### Evaluating the cost-effectiveness of interventions

The cost-effectiveness of implementing the IP-SDM care model will be evaluated over a study period of six months.

From a societal perspective, costs will include those borne by women and health insurance as well as those borne by the hospital. The costs borne by women and health insurance will be estimated based on the predicted values from the regression analysis described above, using data collected from questionnaires. The costs borne by hospitals will be accounted for using the time-driven activity-based costing (TDABC) method [40]. TDABC is a costing method that utilizes the time needed to complete the process to produce a product or deliver a service. In healthcare settings, TDABC is often implemented using seven-step approach, as follows: select the health condition; define the care delivery value chain; develop process maps that include each activity in patient care delivery, and incorporate all direct and indirect capacity-supplying resources; obtain time estimates for activities and resources used; estimate of all direct and indirect resources involved in care delivery; estimate the capacity of each resource and calculate the capacity cost rate (e.g., a cost per unit of time); calculate the total cost of patient care by multiplying the total time of care delivery by the capacity cost rate [41].

In the cost-effectiveness analysis, the effectiveness will be calculated based on the number of women who score 13 or higher on the EPDS at 6 months post-baseline. To compare the cost-effectiveness of between the intervention and control groups, the incremental cost-effectiveness ratio (ICER) will be calculated as the difference in cost between the two groups divided by the difference in their effectiveness.

In addition, the utility will be calculated based on QALYs converted from health-related quality of life as measured by the SF-6D at 6 months post-baseline. ICER will then be calculated as the difference in cost between the intervention and control groups divided by the difference in their QALYs.

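### The economic evaluation is called societal, but participant costs are limited to seeking mental health care, so work lost to depression and other care it causes are left out

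*Protocol article*

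**What the plan says.** Under Statistical analysis, the section on evaluating cost-effectiveness sets the perspective: "From a societal perspective, costs will include those borne by women and health insurance as well as those borne by the hospital". The analysis covers six months. The same cost difference feeds two ICERs, one with an effect based on the number of women at or above 13 on the EPDS at six months, the other with QALYs from the SF-6D.

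Table 1, Cost row, describes the participant instrument. Its overall purpose is to "measure the costs associated with maternal mental health service seeking". Its three components are:

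- medical: "direct medical costs, including the costs of maternal psychiatric services, psychotherapy, counseling, etc";
- non-medical: "transportation and accommodation fees for maternity and their companions seeking mental health services";
- productivity: "indirect costs, including labor losses such as lost wages for maternity and their companions as a result of seeking mental health services".

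A second questionnaire, for staff and administrators, covers "the cost of conducting the interprofessional shared decision-making model and subsequent mental health services". The Follow-Up Survey paragraph lists service utilization and its associated costs at one, three and six months, and no separate item on work loss. In the analysis, "The costs borne by women and health insurance will be estimated based on the predicted values from the regression analysis described above", using the questionnaire data.

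**The concern.** A societal perspective is normally understood to include the production lost through the illness itself, not only the time spent obtaining care for it. Here a lost working day counts if it was spent attending a mental health service and does not count if the woman could not work because of her symptoms. Other health care used because of depression is likewise outside the questionnaire's scope.

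The omission need not be neutral between arms. The Background hypothesises a "positive impact on the quality of the decision-making process, mental health service utilization, and mental health outcomes". If that is right, the plan records the cost of delivering the model and of each added contact, but not the work loss or other care that fewer symptoms would avert. Both ICERs use that cost difference, and the Discussion says that the economic result is meant to help future dissemination. A reader of a societal ICER would assume that such offsets had been counted.

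**Working it through.** The protocol states no cost, wage or work-loss figure, so there is none to reproduce. The check sets the declared perspective against what the instruments collect, then shows how the omission acts on the cost difference.

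**1. Scope**

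| Cost item | Collected? | Source |
|---|---|---|
| Mental health services (women, insurance) | Yes | Table 1, participant questionnaire |
| Travel and accommodation for that care | Yes | Same |
| Wages lost while seeking that care | Yes | Same |
| Running the model and providing subsequent mental health services | Yes | Table 1, hospital questionnaire; time-driven costing |
| Work lost because of symptoms | No source named | – |
| Other health care used because of symptoms | No source named | – |

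The word introducing the list of indirect costs leaves it slightly open, but the sentence giving the questionnaire's purpose governs every component and closes that gap.

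**2. Effect on the cost difference**

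Let ΔC be the planned incremental cost per woman, W the daily wage, d the symptom-related working days averted per woman, and H the other health care cost averted per woman. Then

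societal ΔC = planned ΔC − W × d − H.

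Planned ΔC is too high by W × d + H when that sum is positive, and correct when it is zero. For a favourable effect ΔE, either ICER is too high by (W × d + H)/ΔE.

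**3. Illustration**

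All values here are assumptions, in units of one daily wage, with H = 0. Suppose that one contact costs 1.0 (fee) + 0.2 (travel) + 0.5 (time) = 1.7, and that the intervention adds two contacts. Planned ΔC from these contacts is 2 × 1.7 = +3.4.

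| Days averted, d | Planned ΔC | ΔC counting symptom-related work loss |
|---|---|---|
| 0 | +3.4 | +3.4 |
| 1 | +3.4 | 3.4 − 1 = +2.4 |
| 2 | +3.4 | 3.4 − 2 = +1.4 |
| 5 | +3.4 | 3.4 − 5 = −1.6 |
| 10 | +3.4 | 3.4 − 10 = −6.6 |

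The sign changes once d exceeds 3.4 days. With one or four extra contacts the break-even is 1.7 or 6.8 days. The cost of running the model is left out of this sketch.

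**4. Does more treatment always mean higher recorded cost?**

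No. The Study site section describes both on-site care and off-site psychiatric referral. Assume four on-site contacts at 0.5 + 0.1 + 0.25 = 0.85 each, and two off-site contacts at 1.5 + 0.5 + 1.0 = 3.0 each. The totals are 4 × 0.85 = 3.4 and 2 × 3.0 = 6.0, so the arm with more contacts is cheaper under the plan's own definition.

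**The case against.** The strongest reply is that this is only a label, and that the protocol openly lists whose costs it counts. Several parts of that defence stand.

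- A reader might infer that the arm with more treatment can only look more expensive. The documents do not support that. Service mix and unit costs count, costlier mental health care averted within six months is recorded as a saving, and the Background itself calls the effect of shared decision-making on resource use controversial.
- A reader might also infer that an untreated woman costs nothing. At most that describes the participant questionnaire. Hospital costs remain: usual care includes a nurse call-back after a positive screen, and intervention women also receive the decision aid and coaching.
- Some loss of functioning does reach the analysis, through the role limitation and social functioning dimensions of the SF-6D. It enters only the QALY ICER, as utility and not as cost.
- Employment and leave in this pregnant and postpartum population are not described, so averted paid days could be few.
- The cost scale is unfinished and the article is condensed.

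The last point does not dispose of the matter. The article is not silent here: it states the condition under which lost wages count, and that condition is narrower than the perspective it declares. Listing the cost bearers does not cure this, because a woman also bears wages lost through illness, and those are not collected.

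**Conclusion.** The point holds as a mismatch between the declared perspective and the costs measured. Symptom-related work loss and other care caused by symptoms are outside the cost total. If the intervention reduces them, incremental societal cost is overstated by exactly the amount averted, and both ICERs are less favourable to it than they should be. If they do not differ between arms, the ICERs are unbiased on this account and only the label is too broad.

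The direction is therefore conditional on an effect that the trial has yet to show, and the size is unknown. The day counts and unit costs in the illustration are assumptions and estimate nothing about this trial. The issue concerns a secondary economic outcome; the primary outcome, decisional conflict at one month, and the sample size are unaffected. It should be settled before follow-up starts, because work loss not asked about at the time can later be recovered only by recall.

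**What to change.** Do one of two things.

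1. **Measure it.** While the questionnaire is being developed, add a few items at one, three and six months on paid work lost because of depressive symptoms and on other health care used because of them. Report the cost total and both ICERs with and without these items. Keep lost usual activity out of the cost side of the QALY ICER, or show it only as a sensitivity analysis, because SF-6D role limitation may already capture it and the loss would be counted twice. The cost is a slightly longer interview and some recall error.
2. **Rename it.** In the cost-effectiveness section, replace the societal perspective with: costs of mental health service seeking and provision (women, health insurance, hospital). Limit the cost-effectiveness conclusion to that scope. This is a one-line change, but it gives up any societal claim.

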**Control variables**		
	Decision-making preferences	Decision-making preferences will be measured by the Control Preference Scale, which is commonly used to measure patients’ willingness preferences to participate in healthcare decision-making. The scale consists of 5 entries that can classify patients into 3 types: active decision makers, negative decision makers, and shared decision makers.
	Mental health literacy and stigma	The Multicomponent Mental Health Literacy Measure (MMHLM), which is commonly used internationally, is applied in this study to measure maternal mental health literacy and stigma. The 22-item MMHLM, which contains three dimensions of knowledge, beliefs, and resources, has good reliability and validity, is suitable for assessing mental literacy in adult populations, and is also a good predictor of mental health service utilization behavior. The Chinese version of the questionnaire has been tested for reliability and validity in a domestic population.

**Baseline Survey**: After obtaining informed consent, a member of the research team will conduct a baseline survey. This survey will include basic maternal personal information (e.g., age, education, marital status, family health history, health insurance), level of decisional conflict, history of mental health service utilization, mental health literacy and stigma, and decisional preferences. Among them, basic demographic and health information (e.g., family health history) will be compared with electronic health records for confirmation.**Follow-Up Survey**: Follow-up surveys will be conducted at one, three, and six months after baseline. These surveys will include measures of shared decision-making (at one month only), decisional conflict, depressive symptoms, mental health service utilization, and associated costs. The primary outcome of this study is the level of decisional conflict one month after baseline.

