### ① Study site

This study will select the Obstetrics & Gynecology Hospital of Fudan University as the study site for the RCT. The Obstetrics & Gynecology Hospital of Fudan University is one of the largest obstetrics & gynecology hospitals in Shanghai, providing both primary and specialty maternal care to more than 10,000 women annually. The hospital is also the first maternal health institution in Shanghai to routinely provide PND screening and mental health services. Mothers are screened for depression at different stages of pregnancy (first, second, and third trimester), before discharge after delivery, and six weeks after delivery, during their routine maternal care. A stepped care model is implemented accordingly as follows.

EPDS score < 9: The maternal care provider will provide health education on mental health issues and inform the mother of the relevant resources.9 ≤ EPDS score < 13: The maternal care provider will recommend the mother to schedule the on-site outpatient counseling services provided by the hospital.EPDS score ≥ 13: The maternal care provider will record the EPDS score in the outpatient health record and discuss treatment options with the mother. If in need, the mother will receive further on-site mental health services through a multidisciplinary team (MDT) approach. Alternatively, she may receive off-site mental health services via referral to psychiatric hospitals. A nurse specialized in perinatal mental health will call the mother back within a week and recommend a follow-up visit to the on-site outpatient counseling services if the diagnosis of any mental disorders is not confirmed. Otherwise, if the diagnosis is confirmed, the mother will be managed by a collaborative care team consisting of an obstetrician, a psychiatrist, and a nurse specialized in perinatal mental health.

Few obstetrics & gynecology hospitals or maternal and child healthcare institutions in China have integrated the screening and intervention for PND in routine maternal care. This hospital is selected as the study site to ensure that mothers with mental health needs could access relevant services during the study.

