### ② Study population and recruitment

The study population consists of expectant and new mothers (up to six weeks after delivery) who have screened positive for PND (EPDS score ≥ 13). EPDS usually identifies mild depressive symptoms with a threshold of 9 and moderate to severe depressive symptoms with a threshold of 13 [4]. The current study site routinely uses 13 as the threshold to identify patients with possible moderate to severe PND. This group of patients is included as the study population as they may be particularly at risk if they are not treated or monitored for symptoms.

The research team will recruit women who screen positive for PND at the outpatient maternal care clinics where women visit for routine maternal checkups. Women who have delivered for more than six weeks are not included as they were only followed up by maternal care providers until six weeks after delivery in routine maternal care. Each mother interested in participating in this study is required to sign an informed consent form. The process of enrollment is shown in Fig. 2.

The Inclusion and exclusion criteria for the study population are as follows.

Inclusion criteria: 18 years of age or older; a local resident in Shanghai; a registered client at the selected study site to receive maternal health services; and an EPDS score ≥ 13 during pregnancy or within seven weeks postpartum.Exclusion criteria: suffering from serious mental illness, namely schizophrenia, delusional disorder, schizoaffective disorder, bipolar disorder, psychotic disorder due to epilepsy, and mental retardation with psychotic symptoms; suffering from other diseases that require immediate hospitalization.

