### ⑦ Statistical analysis

#### Evaluating the effectiveness of interventions

Quantitative data will be analyzed using STATA according to the principles of intention-to-treat analysis. This study will use t-tests, chi-square tests, and hierarchical generalized linear models to compare the differences in outcomes between the intervention and control groups. For outcome indicators measured at the same time point (e.g., at one month after baseline), t-tests and chi-square tests will be used to compare continuous variables (e.g., level of decisional conflict) and categorical variables (e.g., mental health service utilization), respectively. In contrast, for outcome indicators (e.g., depressive symptoms) that are repeatedly measured at different time points throughout the study period, hierarchical generalized linear models will be used to estimate fixed effects of treatment factors and individual-level random effects.

In addition, this study will use causal mediation analysis to estimate how the levels of SDM affect multiple outcome indicators of patients in the intervention group and the control group, using whether they belong to the intervention or control group as an instrumental variable. Causal mediation effects can be estimated by regression models, depending on the type of exposure, mediator, and outcome variables (whether dichotomous or continuous) and whether the mediating variable interacts with the exposure variable [38]. Analysis of causal mediating effects can also be combined with instrumental variables [39] to analyze the mechanisms by which the levels of SDM itself contribute to multiple patient outcomes.

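### The listed baseline survey omits the EPDS and the depressive-symptoms model is described without a baseline EPDS term, although every participant must have a qualifying score on record

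*Protocol article*

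**What the plan says.** All references are to the protocol article.

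- **Baseline survey** (⑥ Measurements, text after Table 1): personal information, then "level of decisional conflict, history of mental health service utilization, mental health literacy and stigma, and decisional preferences". The EPDS is not named.
- **Follow-up surveys** (same place; one, three and six months): shared decision-making at one month only, then "decisional conflict, depressive symptoms, mental health service utilization, and associated costs". Decisional conflict is therefore listed at baseline and follow-up, but depressive symptoms at follow-up only.
- **Instrument** (Table 1, secondary outcomes): "Women’s depressive symptoms will be measured by the EPDS, a 10-item maternal self-report of depression over the past 7 days".
- **Control variables** (Table 1): two entries, decision-making preferences, and mental health literacy and stigma. Baseline depression severity is not among them.
- **Model** (⑦ Statistical analysis): for repeatedly measured outcomes, with depressive symptoms as the example, "hierarchical generalized linear models will be used to estimate fixed effects of treatment factors and individual-level random effects".
- **Entry** (② Study population and recruitment): an EPDS of 13 or more "during pregnancy or within seven weeks postpartum".
- **Routine care** (① Study site): at 13 or more, "The maternal care provider will record the EPDS score in the outpatient health record".
- **Cost-effectiveness**: effectiveness is based on the number of women at or above 13 on the EPDS six months after baseline.

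**The concern.** Women enter with any score from 13 upwards, so severity at entry varies, and it can be expected to predict later scores. The section on randomization describes permuted blocks and names no stratification factor, so the design itself does not balance severity. A baseline EPDS covariate would remove part of the outcome variance and correct for chance imbalance. As written, the plan neither lists a baseline measurement nor names the term.

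The measurement matters more than the model sentence. An analysis plan can add a covariate later, but it cannot recover an EPDS that was not collected at enrolment. The screening score is a weaker substitute. The instrument covers the past seven days, while the qualifying score may come from any time in pregnancy or the early postpartum weeks, and no maximum interval to enrolment is stated.

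At stake is the precision of the estimated effect on depressive symptoms and on the share of women at or above 13 at six months, the denominator of the first cost-effectiveness ratio.

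**Working it through.** **1. The plan's own figure (④ Sample size).** Inputs: two-sided α 0.05, z values 1.96 and 0.84, standardised difference 0.3, dropout up to 15%.

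- n per group = 2 × (1.96 + 0.84)² / 0.3² = 174.2, stated as 174.
- 174 / 0.85 = 204.7, so 205 per group and 410 in total.

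Both figures reproduce. They rest on decisional conflict at one month, so this point does not touch them. The article gives no effect size, SD, correlation or power for the EPDS.

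**2. Precision at a single visit (illustration).** Assumptions: EPDS standardised difference 0.3 (borrowed from decisional conflict), 174 per group analysed, and baseline to follow-up correlation r of 0.2 to 0.5. Truncating entry scores at 13 tends to lower r, which is why the range starts at 0.2.

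Residual variance ratio = 1 − r². Power = Φ[0.3 / √(1 − r²) × √(174/2) − 1.96].

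| r | variance removed | power | n per group for 80% power |
|---|---|---|---|
| 0 (no covariate) | 0% | 79.9% | 175 |
| 0.2 | 4% | 81.5% | 168 |
| 0.3 | 9% | 83.5% | 159 |
| 0.4 | 16% | 86.3% | 147 |
| 0.5 | 25% | 89.8% | 131 |

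The unadjusted n is 175 here and 174 in the plan because the z values are not rounded.

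**3. Average over three visits.** The planned EPDS model is longitudinal, so a second illustration uses the mean of the three visits. Let ρ be the assumed correlation between follow-up visits, and let r be the same at each visit. The unadjusted variance is (1 + 2ρ)/3, and the adjusted variance is that minus r².

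- ρ = 0.6, r = 0.3: 0.733 falls to 0.643; power goes from 90.5% to 93.7%.
- ρ = 0.6, r = 0.5: 0.733 falls to 0.483; power goes from 90.5% to 98.1%.

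Power starts higher, so there is less to gain in power points, but the covariate still removes variance.

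**4. Chance imbalance.** With 205 per group, the standard error of the baseline difference is √(2/205) = 0.099 SD, so the 95% range is ±1.96 × 0.099 = ±0.19 SD. An imbalance at that limit shifts an unadjusted follow-up difference by r × 0.194: 0.04 SD at r = 0.2 and 0.10 SD at r = 0.5. Against an effect of 0.3 SD that is 0.039/0.3 = 13% and 0.097/0.3 = 32%.

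**The case against.** The strongest case against runs as follows. The article condenses a fuller plan, and its model sentence covers all repeatedly measured outcomes without listing or excluding covariates. Table 1 has a block of control variables, so some adjustment seems intended. Covariate lists commonly belong to the analysis plan, which is not shown. The assessment schedule, Fig. 3, is not shown either and may list the EPDS at enrolment. The outcome is secondary, and the primary outcome does have a baseline measurement.

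Much of this stands, and it rules out several stronger readings that a reader might infer:

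- **That the EPDS will be analysed unadjusted, or that the screening score is never used.** The text is silent; it states neither. The score is used for eligibility.
- **That the comparison is biased.** With random allocation it is not.
- **That the EPDS is the key outcome.** It is one of several secondary outcomes.
- **That leaving out severity undermines the missing-data assumption.** Severity may well predict dropout, but nothing in the article shows it. A likelihood-based mixed model also uses EPDS scores already observed, so only dropout before the one-month survey depends wholly on baseline data.
- **That the power gain is a property of this trial.** The correlation and the EPDS effect size are both assumed.

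The objection does not dispose of the measurement. The baseline instruments are listed by name, and the examples given in that list qualify only the personal and health information. What is collected at enrolment is a matter for the protocol, and a later analysis plan cannot supply it.

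**Conclusion.** The point holds in limited form. The baseline survey as listed does not include the EPDS, and the model for depressive symptoms is described without a baseline EPDS term, while a qualifying score must exist for every participant. Validity is not in question. The cost is avoidable noise and exposure to chance imbalance in one secondary outcome and in the six-month threshold measure derived from it.

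The size depends on a correlation that the article does not give. Over 0.2 to 0.5, the single-visit gain runs from under 2 to about 10 power points. At the lower end it is small, and an old screening score used as baseline would probably sit nearer that end. The sample size of 174 per group and 410 in total is unaffected. The change is worth making because it is cheap and because a baseline missed at enrolment cannot be recovered. If Fig. 3 already shows the EPDS at enrolment, what remains is to align the text and name the covariate.

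**What to change.** 1. Add the ten-item EPDS to the face-to-face baseline survey and complete it before the allocation envelope is opened. The article places both after consent but does not state their order.
2. At minimum, import the qualifying score and its date from the outpatient record, and acknowledge that it is a weaker baseline because no maximum interval to enrolment is stated.
3. Prespecify the continuous baseline score as a covariate in the EPDS mixed model and in the analysis of EPDS 13 or higher at six months. Use the continuous score: dichotomised at 13, the qualifying score is the same for every participant.
4. Align the baseline survey text, Table 1 and Fig. 3.

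The cost is ten self-report items at a contact already planned, or a record extraction, plus one model term. No change to recruitment is needed.
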